## Abstract

**Background:**

Mental disorders (MD), such as depression, anxiety, and cognitive impairment, are highly prevalent in patients with coronary heart disease (CHD). Current guidelines on cardiovascular diseases recommend screening and appropriate treatment of MD; however, the degree of implementation of such recommendations in clinical practice is unknown. This study aims to analyze the quality of health care of patients with CHD and MD. Specifically, we aim to analyze (1) the quality of care, (2) trajectories of care, and (3) barriers regarding the detection and treatment of MD. Moreover, we want to identify potentials of changes in health care delivery towards more patient-centered care. The results of this study shall be the first step towards value-based care of people with CHD and comorbid mental disorders.

**Methods:**

We aim to include the following participants: adult patients with CHD (*n* = 400), their relatives (*n* = 350) and physicians (*n* = 80). A particular focus will be on the vulnerable subgroups of patients with CHD and congestive heart failure (left ventricular ejection fraction < 40%) and on the underrepresented group of women with CHD. We will apply a mixed-method approach with a quantitative and a qualitative part.

Patient-related outcomes (e.g., health-related quality of life, needs, and preferences regarding health care, reasons for non-detection, and lack of treatment of MD) will be explored in a multi-perspective approach including patients, relatives, and physicians’ perspectives. Furthermore, routine data from four statutory health insurance funds (SHI) will be analyzed regarding the frequency and treatment of MD in CHD patients.

**Discussion:**

MenDis-CHD will provide important insights into the trajectories of health care, quality of health care, barriers, patient needs and preferences as well as expectations and satisfaction with health care in patients with CHD and MD. Potential implications of MenDis-CHD are to enable health care providers to redesign care pathways concerning the treatment of mental comorbidity in patients with CHD by proposing value-based changes in health care and by understanding the barriers to and facilitators of change towards patient-centered care.

**Trials registration:**

German clinical trials register (Deutsches Register Klinischer Studien, DRKS) ieRegistration Number: DRKS00012434, date of registration: May 11th, 2017.

## Background

Coronary heart disease (CHD) is the leading cause of morbidity and mortality in Europe and the USA [1, 2]. In 2008, approximately 17 million people died worldwide from CHD, and 10% of the burden of disease worldwide is caused by CHD [3]. Due to advances in the acute treatment of CHD, short-term mortality has decreased, but morbidity on a population level has increased [1, 2, 4]. In recent years, gender aspects concerning CHD received increasing attention. Men have a twofold higher CHD prevalence (12.3%) than women (6.4%) [4, 5]. However, there is a stronger increase in incidence in older women compared to men [4]. CHD-related mortality in women also appears to be slightly higher [5]. Several reasons have been discussed, including the older age of women at the acute cardiovascular event, but also lower detection rates and less treatment of cardiac symptoms [5, 6]. Also, mental disorders (MD) have been found to be highly prevalent among patients with CHD, particularly in women [7]. Especially depression, anxiety disorders, cognitive impairments [8] and other MDs affect approximately 50% of all CHD patients [7, 9, 10].

MD – whether they are pre-existing conditions or consequences of CHD – act as particularly strong barriers to treatment adherence and impede efforts to lifestyle change [1], resulting in an approximately two-fold greater morbidity and mortality risk in CHD [1, 7, 9, 11, 12].

In detail, several mechanisms are discussed: first, unhealthy lifestyle (e.g., smoking, high alcohol consumption) is more prevalent in patients with CHD and MD. Second, CHD-patients with MD are more resistant to behavior change and have low medication adherence. Third, psychobiological mechanisms are found, which increased risk for CHD, even if the ‘classical’ risk factors are controlled for (e.g., alterations in autonomic functions, in the hypothalamic-pituitary axis and in inflammatory markers [13]). The prevalence of depressive symptoms in CHD patients is approximately 31% in women and 20% in men. Anxious symptoms occurred approximately in 39% of the women and in 22% of the men 1.4 years after hospitalization for CHD [14]. Consequently, recent, national and international guidelines on primary and secondary prevention of CHD recommend routine screening for MD and adequate treatment for at-risk patients [1, 10, 15].

Given that adherence to CHD guidelines in physicians is generally low, even when these guidelines predominantly comprise somatic recommendations [16], it is unlikely that general practitioners and cardiologists regularly screen for MD due to typical restraints such as a lack of time and low reimbursement of verbal interventions [12, 17]. However, a systematic review in 2013 showed that depression screening is only beneficial for identifying depressed patients that were not already diagnosed or treated for depression. Also, the accuracy of screening tools seems to be exaggerated by the inclusion of already diagnosed patients and the selective reporting of results from cut-off scores. Following this review, a wide range of routine screening would entail high costs and increase the number of patients using antidepressants. Hence, it is important to not only look at the screening for MD and cognitive impairements but also to look at diagnostic and treatment following the screening [18]. Overall, the status of quality of care in CHD patients with comorbid mental disorders is unknown. Moreover, it is unclear what the trajectories of care of patients with CHD and cognitive impairement are.

In addition, no data on personal preferences, needs, and expectations of patients with CHD and their relatives regarding the detection and treatment of MD have been published. Thus, there is an urgent need to explore the current state of care in patients with CHD and MD to identify relevant factors that are preventing improved care in health care systems.

## Methods

### Aims

The study examines [1] the current quality of health care regarding to the detection and treatment of MD in patients with CHD, [2] the experiences of physicians in treating their patients according to guideline, [3] needs and preferences of the patients and [4] possible barriers for the implementation of guideline-based diagnostic and treatment.

Further, routine data from health insurance funds (SHI), collected continually for reimbursement and stored for several years by health insurers, will be allocated [19]. The SHI-data will be analyzed concerning frequency of CHD as well as sex and age distribution, use of the resource, costs, and trajectories of care (e.g., diagnosis of MD, psychotropic medication, psychotherapy, hospital stay, sick leave certificates, and early retirement).

The findings of the MenDis-CHD will contribute to an overview of the current state of health care in CHD with the aim of improving and modifying care delivery, so that appropriate interventions ensure value-based health care.

### Theoretical framework and research platform

MenDis-CHD is located in Cologne, Germany and is one of three current projects of the ‘Cologne Care Research and Development Network’ (CoRe-Net). Core-Net is funded by the Federal Ministry of Education and Research (BMBF), and the MenDis-CHD study protocol was subject to peer review by the funding body before approval. The value-based health care concept by M.E. Porter [20–22] forms the framework of CoRe-Net, which has the aim to create a data-driven learning environment employing research and practice to improve health and social care organizations by transforming them into a system that develops and delivers care with greater value. We define value-based health care as cost-consciously redesigning care processes and structures according to the needs of patients, which includes the two dimensions of patient-related and economic aspects. For further details about CoRe-Net see [23].

### Participants of MenDis-CHD

Overall, we aim at recruiting a total number of *N* = 830 participants. The total sample includes subsamples of patients, relatives, and physicians. Since Jan 15, 2018, the MenDis-CHD study is in the recruitment phase.

#### Patients

We intend to enroll adult patients (*n* = 400; 50% women) with angiographically documented CHD treated for stable angina pectoris, acute coronary syndromes, percutaneous coronary intervention, or bypass surgery. Participants must be able to give informed consent and have sufficient German language skills. Exclusion criteria are severe or instable physical or mental conditions (e.g., severe illnesses such as cancer, acute suicidal ideation, delirium, and moderate to severe dementia). Since we are conducting a descriptive and exploratory study, but not a confirmatory one, we did not performed a sample size calculation based on a power calculation. Rather the focus of MenDis-CHD is on vulnerable subgroups. These vulnerable subgroups comprise (1) older female CHD-patients which were underrepresented in past studies, (2) CHD-patients with comorbid mental disorders and/or mild cognitive impairment (expected prevalence of MD and MCI is 30–50%), and (3) CHD-patients with congestive heart failure (expected prevalence of 30% with a left ventricular ejection fraction of < 40% [24]). To obtain a realistic estimate of the health care situation, patients will be recruited in cardiology departments of hospitals, cardiology practices, and rehabilitation clinics.

Thus, the rational for the intended sample size are this estimated frequency of the gender distribution, mental and cognitive comorbidity and patients with congestive heart failure as well as the goal of recruiting in different sectoral areas (hospitals, rehabilitation clinics, and cardiology practices). By this rationale, we aim at a sufficiently large sample sizes to perform the statistical comparison in these vulnerable subgroups. In sum, the recruitment of a total *N* of 400 patients is planned. Thus, we aim to recruit *n* = 200 women, *n* = 130–200 patients with MD or MCI and *n* = 120 with congestive heart failure.

All 400 patients (with and without MD) will take part in the quantitative study. *N* = 20 participants of the patient sample will be invited to join qualitative interviews.

#### Relatives

We aim at recruiting a total number of *n* = 350 relatives of the CHD patients for the quantitative survey. Of these, *n* = 20 will be asked to participate in qualitative interviews. The group of relatives is defined as every close person living in the household of the patients. Inclusion criteria for relatives are: 18 years of age or older, able to give informed consent and sufficient German language skills. Exclusion criteria are severe or instable physical or mental conditions.

#### Physicians

A total number of *n* = 80 physicians (general practitioners (GPs), cardiologists, physicians at rehabilitation clinics, and psychotherapists) will be tried to be recruited for a quantitative assessment. *N* = 20 physicians of this sample will also participate in qualitative interviews. Moreover, *n* = 40 physicians will be randomly selected to participate in focus groups. Four focus groups, each consisting of ten participants will be conducted, including following specialties named above.

Please refer to Fig. 1 for details on the recruitment procedure and sub-samples.

**Fig. 1 Fig1:**
[figure not shown]
Flowchart of the study population divided into three sub populations with the detailed procedure. CERAD: Consortium to Establish a Registry for Alzheimer’s disease; CHD: Coronary Heart Disease; DemTect: Demenz-Detection-Test; EQ-5D: EURO-Quality of Life 5D; FAQ: Functional Activities Questionnaire; GPs: General Practitioner; HADS-D: Hospital Anxiety and Depression Scale; LVEF: Left Ventricular Ejection Fraction; PACIC: Patient Assessment of Care for Chronic Conditions; SKID-I: Structured Clinical Interview for DSM-IV

#### Study population of SHI data

SHI data of patients who are inhabitants of Cologne continually insured between 2011 and 2012 and continually insured or deceased in 2013 through 2015 in one of the four participating health insurance companies - (estimated about 270,000 persons) will be provided.

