##### Statutory health insurance data (SHI)

Secondary claims data will be provided by four major health insurances of the state of North Rhine-Westphalia in Germany, from 2011 to 2015, for insuree living in Cologne. This SHI data is part of the CoRe-Net-database and will be used for this project (https://www.core-net.uni-koeln.de/index.php/de/core-net-datenbank/). Besides master data (e.g., age, sex, insurance status and period of insurance) information concerning the use of all sectors of care (inpatient and outpatient care, drug prescription, benefits in kind, long-term care) will be available and connectable by a non-identifiable study number. In detail, ICD-10 coded diagnoses from out- and inpatient care, medical services according to the EBM-Code (German physician fee manual), hospital stays with length of stay and OPS-procedures (Operations and Procedures Key), drug prescription with pharmaceutical registration number and linkage to ATC-Code (Anatomical Therapeutic Chemical Classification System) and DDD (Defined Daily Dose Classification), as well as information concerning inability to work (diagnosis, duration) and utilization of long-term care will be provided. For all services, provided SHI cost data will be available. Spatial data (e.g., INKAR: Indicators and maps for area- and town development) could be added.

In a first step, quality and plausibility checks of the SHI-data are performed. In a second step, patients with CHD and MD are identified by their diagnoses, which will be internally validated [44]. Inclusion criteria for CHD patients will be a hospital discharge diagnosis of CHD (ICD 10-GM code I20- I25), for chronic heart failure patients (ICD 10-GM code I11.0, I13.0, I13.2, I50), an outpatient diagnosis in at least two quarters of a or a hospital discharge diagnosis and for MD-patients (ICD 10 GM-code F00-F99, and more specific: F06.7, F32, F33) in one quarters of year or a respective hospital diagnosis. We will apply a cross-sectional design for basic epidemiological data (e.g., frequency of CHD, CHD, and MD, psychotherapy, mortality) and a cohort design for the analysis of care trajectories starting in 2013, allowing a pre-observation period and a follow up of at least 2 years each.

These SHI-data will enrich the empirical part of the study [19] [45] as it allows to compare characteristics of general CHD-population with MD identified in the data to those included into the study and to determine the possible selection bias.

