#### Qualitative

The qualitative module aims to analyze profoundly the patients’ needs, preferences, attitudes, and barriers regarding value-based care of CHD patients with comorbid MD. The overall research question of the qualitative module focuses on the trajectories of care and quality care of the CHD-patients, relatives, and physicians. In how far are their expectations met and which barriers are they facing?

Overall, outcomes of the patients’ data are: (1) prevalence of MD, (2) types of diagnostic procedures and treatment received, (3) quality of life, (4) satisfaction and short comings with respect to trajectories and quality of health care, and (5) expectations and needs with regard to health care (patient preferences). The outcomes will be analyzed separately for age groups and gender.

Main outcomes for the relatives’ data are: (1) frequency of contact with the health care system and provided care, (2) caregivers’ burden, (3) quality of life, (4) satisfaction with respect to trajectories and quality of health care, (5) patterns of perception about value, and (6) expectations and needs with regard to health care (preferences of relatives).

Main outcomes of the health care professionals’ are: (1) knowledge, attitudes, and experiences concerning guideline recommendations, (2) personal views and experiences regarding MD detection, treatment, and value for the patient, and (3) limitations and barriers in the health care system. Further, outcomes of the focus groups of the health care professionals are about obstacles about guideline adherence, diagnosis and treatment of MD in CHD.

In the SHI data the outcomes of interest are prevalence and incidence of MD diagnosis in CHD patients, documented diagnostics, and treatments (e.g., prevalence of psychotropic medication and/or psychotherapy), documented costs according to sectors of care, as well as treatment persistence, frequency and duration of hospital stay, sick leave certificates, early retirement and death.

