## Discussion

Data will be generated from multiple sources, including claims data, surveys, interviews and focus groups of professionals, patients, and relatives. Thus, our study design adopts a multi-perspective approach, which combines patients, their relatives and physicians views with in-depth analysis of trajectories, quality of health care, needs and preferences by quantitatively and qualitatively methods. Besides, we are able to gain insight into the general treatment of a non-selective population with CHD and MD by using SHI data.

The value-based concept by Porter [20–22] forms the analytical framework for our project. Consequently, our vision is to create value for the patient paying attention to both quality of health care and costs. MenDis-CHD will provide essential insights into the trajectories of health care, quality of health care, barriers, patient needs and preferences as well as expectations and satisfaction with health care in patients with CHD and MD.

The multi-method and multi-perspective approach of MenDis-CHD will provide data-driven analysis tools to enable care providers to redesign care pathways by proposing value-based changes in care and to understand the barriers to and facilitators of change towards patient-centered care. Restructuring complex care for vulnerable CHD patients is very much needed since there is evidence that these patients are underserved and often get lost in the transition between multi-professional and multi-institutional care providers [51, 52]. This generates unnecessary costs, ill health and thus low value for the patient.

MenDis-CHD has already begun to perform workshops inviting our scientific and practice partners, stakeholders, caregivers, patient and relative representatives to develop specific deliveries and methods for value-based health and social care in highly vulnerable patients with CHD and MD. Moreover, we have built up a representative network of recruitment centers. However, practice will have to show how well we succeed in recruiting patients against the backdrop of a significant reduction in inpatient stays. As already noted, women represent a vulnerable subgroup underrepresented in previous studies. Thus, recruitment will have to additionally show how demanding it is to achieve the targeted sample sizes of female patients.

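### Entry to the claims cohort depends on what happens after follow-up starts: deaths under cover are kept and living leavers are removed, so cumulative mortality is modestly overstated

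*Protocol article*

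**What the plan says.** The Protocol article, under Study population of SHI data, restricts the claims data to residents of Cologne who were "continually insured between 2011 and 2012 and continually insured or deceased in 2013 through 2015 in one of the four participating health insurance companies". It estimates about 270,000 such persons.

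Under Statutory health insurance data (SHI), the article plans "a cohort design for the analysis of care trajectories starting in 2013, allowing a pre-observation period and a follow up of at least 2 years" for each person. The same section names mortality among the basic epidemiological measures. It also lists each person's insured period among the master data to be delivered.

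The last paragraph of Outcomes gives further claims outcomes, among them "treatment persistence, frequency and duration of hospital stay, sick leave certificates, early retirement and death".

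Two statements bear on selection. The SHI section intends to use the claims data "to compare characteristics of general CHD-population with MD identified in the data to those included into the study and to determine the possible selection bias". The Discussion expects to "gain insight into the general treatment of a non-selective population with CHD and MD by using SHI data". The article mentions no count of leavers, no censoring at exit and no sensitivity analysis for them.

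**The concern.** A cohort that begins in 2013 should be defined by what is known when follow-up begins. Here membership also depends on status up to the end of 2015, and the two ways of leaving observation are treated differently. A patient with an index stay in March 2013 who changes to a non-participating fund in November 2015 has 32 months of usable data and is removed from the first day. A patient with the same index stay who dies under cover in November 2015 is kept.

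For mortality, this is selection on the outcome. Deaths under cover stay in the numerator, while the survival time of living leavers is lost from the denominator. This is not a detail that an analysis plan can settle later. If the funds never supply the leavers, no analysis can count, censor or recover them. The one selection check that is planned compares survey participants with the claims population, so it takes the claims population as its reference and does not look inside it.

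**Working it through.** **The plan's own figure.** The estimate of about 270,000 persons cannot be reproduced, because no inputs are given. There is also no stated death or leaving rate, so the rates below are assumptions.

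**Model.** Constant death hazard *d*, constant leaving hazard *l*, leaving unrelated to health, horizon *T* = 3 years (2013–2015).

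- Deaths under cover: D = d/(d+l) × [1 − exp(−(d+l)T)]
- Insured and alive at the end: S = exp(−(d+l)T)
- Leavers, removed by the rule: L = 1 − D − S
- Risk in the retained cohort: D/(D+S)
- True risk: 1 − exp(−dT)

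**Mortality with d = 0.05.** True risk = 1 − exp(−0.15) = 13.9%.

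| l per year | D | S | L removed | D/(D+S) | Ratio to true |
|---|---|---|---|---|---|
| 0.02 | 0.1353 | 0.8106 | 5% | 14.3% | 1.03 |
| 0.04 | 0.1315 | 0.7634 | 11% | 14.7% | 1.05 |
| 0.08 | 0.1242 | 0.6771 | 20% | 15.5% | 1.11 |

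The retained-cohort risk equals the true risk only at l = 0. Three years is the longest window. For two years at l = 0.04, D = 0.05/0.09 × (1 − exp(−0.18)) = 0.0915 and S = 0.8353. The apparent risk is then 0.0915/0.9268 = 9.9%, against a true 1 − exp(−0.10) = 9.5%.

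**Second set of inputs.** True three-year mortality 15%; annual leaving proportion *a* converted by l = −ln(1 − a). The apparent risk is 15.2%, 15.4%, 15.6%, 16.0% and 17.2% for a = 1%, 2%, 3%, 5% and 10%. A simulation of 2,000,000 persons at a = 3% gave 15.6% under the rule as written. When leavers were kept and censored at exit, it gave 15.0%.

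**Comparison by mental disorder (MD).**

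- Equal leaving in both groups: a true risk ratio of 2.00 (30% against 15%) reads 1.99 at 2% a year and 1.98 at 5% a year.
- Equal true mortality of 15%, leaving 2% with MD and 5% without: 15.4%/16.0% = 0.96. With the leaving rates exchanged, 1.04.
- Illustration only, with a fourfold difference in leaving (hazards 0.02 and 0.08) and death hazards of 0.10 with MD and 0.05 without: a true ratio of 1.86 reads 1.71 if leaving is lower with MD and 1.99 if it is higher.

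**The case against.** The strongest reply is that the effect is small and mortality is peripheral. At leaving rates of 2% to 4% a year, a true 13.9% moves only to 14.3% or 14.7%. The claims aims centre on frequency, resource use, costs and trajectories, and the study is declared exploratory. This stands as a limit on size. It does not remove the error, because mortality is a declared claims measure and descriptive figures are what this part of the study produces.

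A second reply is that full cover serves the promise of at least two years of follow-up. That is a fair trade-off, but the rule as written already breaks the promise for persons who die early, and it keeps them. Changing the rule could also require a new delivery from four insurers, since the extract belongs to a shared network database.

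Four stronger readings are tempting and are not supported:

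- *Every death is kept.* Only deaths while insured with a participating fund are. Someone who leaves and dies later is lost too. The wording also leaves open whether a switch among the four funds counts as leaving.
- *Mortality contains immortal time from 2011–2012.* The rule admits no deaths in those years, but the article plans no mortality analysis using person-time from them. For the cohort they are the pre-observation period.
- *All follow-up outcomes are biased in a known direction.* For treatment persistence, sick leave, early retirement and costs, the direction depends on how leaving relates to the outcome, and the article does not say.
- *The comparison by MD status is seriously distorted.* That needs leaving to differ clearly between groups, for which the article offers no evidence.

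**Conclusion.** The point holds as a defect in the extraction rule. Eligibility uses information from inside the follow-up window, and living leavers are dropped while deaths under cover are retained. If leaving is unrelated to health, cumulative mortality is overstated at any non-zero leaving rate. In the main illustration (5% deaths a year, three years), the relative overstatement is about 3% to 5% at 2% to 4% leaving a year and 11% at 8%. These sizes rest on constant hazards and assumed rates; the real leaving rate is unknown. If leaving is related to health, the direction for mortality is open as well.

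Ratios by MD status are nearly unaffected when leaving is equal in the two groups. The figures 1.71 and 1.99 show only what a large difference in leaving could do. Describing the claims population as non-selective goes further than the rule allows. The change is worth making: the mechanism is certain, the likely effect is modest, and the loss cannot be repaired once the extract is fixed.

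**What to change.** **Preferred.** Define eligibility as continuously insured through 2011 and 2012 and still insured at the start of follow-up in 2013. Keep everyone who meets this. Follow each person to the earliest of death, end of cover or the end of 2015, and censor non-death exits using the insured-period field already in the master data. State whether a move between the four funds, or out of Cologne, counts as an exit. Describe follow-up as lasting up to the end of 2015 instead of at least two years for each person.

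**If the extract cannot be redrawn.** Obtain from the four funds the number of leavers by age and sex, report mortality with bounds, and drop the non-selective description in the Discussion. In the illustration with l = 0.04, the deaths observed are 0.1315 and the leavers 0.1052 of the starting population. Three-year risk then lies between 13.1% (no leaver dies) and 0.1315 + 0.1052 = 23.7% (all do). Bounds of this kind are wide. Counting each leaver for half the period gives 0.1315/(1 − 0.1052/2) = 13.9%, which matches the true value under the model's assumption that leaving is unrelated to health.

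**Cost.** Follow-up becomes variable, so rates or time-to-event summaries replace simple proportions. The preferred version may need a revised data request to all four insurers. The fallback needs only counts and a change of wording.
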